## 3. Trial Organization and Funding

The DUTCH CCS registry was registered on ClinicalTrials.gov with the registration number NCT04753372 on 15-02-2021. All data are collected in an electronic data capturing system, the electronic case record form, managed by Diagnostic Research and Management. Diagram BV, located in Zwolle, The Netherlands, is responsible for overall trial and data management, as well as for monitoring of the study. An independent physician of the clinical events committee (CEC) reviews and adjudicates all endpoint-related adverse events.

The Department of Cardiology of Isala Hospital, Zwolle, The Netherlands, sponsors the trial with funding from an unrestricted research grant from Bayer (Hoofddorp, The Netherlands). The primary investigators are solely responsible for the conduct of this registry, all study analyses, drafting and editing the manuscript, and its final contents. Diagram BV is the CRO responsible for performing this registry.

No patients or public are involved in the design of the study.

## 4. Discussion

The COMPASS [11] and VOYAGER-PAD [13] trials demonstrated significant benefits associated with DPI in patients with CCS and peripheral artery disease, respectively. Despite a limited number of randomized trials investigating low-dose rivaroxaban in CCS patients, the findings of the COMPASS trial motivated important updates to the current European Society of Cardiology guidelines for managing CCS. These guidelines now advocate for low-dose rivaroxaban in ACS patients who have successfully undergone twelve months of DAPT without bleeding complications. Specifically, the addition of low-dose rivaroxaban to aspirin should be considered for high-thrombotic-risk patients without an increased risk of major or life-threatening bleeding (Class IIa, Level A), and it may be considered for patients with moderately elevated thrombotic risk (Class IIb, Level A).

While real-world clinical practice often deviates from guideline recommendations, there is currently a dearth of real-world data about the potential impact of low-dose rivaroxaban on clinical outcome of CCS patients. Addressing this knowledge gap, the DUTCH CCS registry endeavors to provide valuable insights into the efficacy and safety of low-dose rivaroxaban in conjunction with aspirin. The focus of the study is on clinical practices and outcomes within a CCS patient population that is characterized by both a high thrombotic risk and a low bleeding risk.

Furthermore, although the majority of all ACS patients are treated by PCI, a substantial number of these patients is managed conservatively, representing a noteworthy portion of the entire CCS patient population. Conservative strategies are often employed for frail, elderly patients with multiple comorbidities, a demographic that is underrepresented in most of the randomized controlled trials. This is particularly true for women who are less prone to have obstructive CAD and might derive benefit from alternative treatment strategies as compared to men. Registry data from real-world clinical practice have the potential of providing signals that the use of low-dose rivaroxaban in combination with aspirin may be a viable alternative to single-antiplatelet therapy with aspirin alone.

Thus, the DUTCH CCS registry holds the potential to enhance our understanding of the real-world impact of low-dose rivaroxaban plus aspirin as a secondary prevention strategy in CCS patients with a high ischemic event risk and a low bleeding risk. The findings may offer valuable insights into the efficacy and safety of DPI, providing clinicians and researchers with data for informed treatment decisions, and may ultimately help refine guidelines for the management of CCS patients in routine clinical practice.

The strength of our study lies in its ability to represent patients encountered in daily clinical practice, utilizing broad inclusion criteria within a multicenter design. The COMPASS trial demonstrated that DPI significantly reduced MACE, major adverse limb events, and cardiovascular mortality in patients with stable CAD. Importantly, patients with diabetes mellitus, multivessel coronary disease and PAD derived the greatest absolute benefit, suggesting that DPI may be particularly effective in individuals with multiple high-risk features. These findings support the rationale for targeting patients with complex atherosclerotic disease who are at heightened thrombotic risk. In our registry, we included patients with PAD only when CAD was also present. This approach reflects current clinical understanding that the coexistence of CAD and PAD identifies a subgroup at especially high risk of ischemic events. We excluded patients with PAD in the absence of CAD, as their risk profiles and clinical management strategies may differ substantially, and they fall outside the focus of CCS as defined in our study. Our inclusion strategy aimed to better reflect the heterogeneity of patients encountered in routine clinical practice, as opposed to the narrow selection criteria used in randomized controlled trials. Data from the CLARIFY registry further justify this broader approach. CLARIFY showed that patients with higher CHA_2_DS_2_-VASc scores—even in the absence of atrial fibrillation—had increased long-term cardiovascular risk. By including patients with elevated CHA_2_DS_2_-VASc scores, our registry captures a wider range of real-world high-risk patients who may benefit from DPI but are often underrepresented in randomized controlled trials.

This pragmatic design allows the DUTCH CCS registry to evaluate the safety and effectiveness of DPI in a patient population that more closely mirrors everyday cardiology practice, improving the generalizability and clinical relevance of our findings.

However, there are several limitations inherent to the registry. One important limitation of this study is its single-arm, open-label design, which precludes direct comparison with a control group and limits causal inference. However, the decision to conduct the DUTCH CCS registry as a single-arm, observational study was deliberate, based on pragmatic and ethical considerations. Our objective was to capture real-world prescribing behavior and treatment outcomes in a high-risk CCS population eligible for DPI with rivaroxaban and aspirin. Importantly, the registry included prospectively defined inclusion and exclusion criteria, ensuring a well-characterized, guideline-eligible patient cohort rather than an unselected population. This structured approach enhances the internal validity of the findings while preserving external generalizability to routine clinical practice. While the absence of a comparator arm remains a limitation, it also avoids the artificial constraints and selection filters often imposed by randomized controlled trials. To address this limitation, future post hoc analyses using historical controls or propensity-score matching are under consideration. These methods may allow for contextualization of outcomes, provided that robust external datasets with compatible eligibility criteria and endpoints become available. At the time of study initiation, such data were lacking. Nevertheless, we believe that the DUTCH CCS registry provides valuable insights into DPI use across a broad and representative patient group, complementing evidence from randomized trials and helping to inform clinical decision-making in everyday practice.

Another potential limitation of this registry is the possibility of selection bias, as patients were enrolled based on predefined inclusion and exclusion criteria, but also at the discretion of the treating physician. However, it is important to clarify that the decision to initiate DPI was made independently of the registry, as part of routine clinical care. Patients were not prescribed DPI in order to participate in the registry; rather, only patients who had already been prescribed DPI based on clinical indication, and who fulfilled the inclusion criteria, were subsequently approached for participation. This approach reflects a real-world, pragmatic design aligned with the non-WMO (non–Medical Research Involving Human Subjects Act) classification of the study. To enhance representativeness and reduce potential selection bias, several quality assurance measures were implemented. All participating centers were instructed to include patients consecutively based on clear eligibility criteria. Additionally, retrospective verification of outpatient clinic records was performed at several sites to ensure that no eligible patients were unintentionally missed. Furthermore, audits and source data verification were conducted by an independent clinical research organization to assess adherence to inclusion criteria and to verify data quality. In cases where a patient was included but later found to be ineligible, the treatment plan was re-evaluated, and if DPI was deemed inappropriate, treatment was discontinued or the patient was excluded from the final analysis. While these procedures cannot entirely eliminate selection bias, they help to mitigate its extent and enhance the generalizability of our findings. Ultimately, our design aimed to capture real-world treatment patterns in a clearly defined, high-risk CCS population while maintaining scientific rigor within the practical and ethical constraints of an observational, non-interventional study. To further minimize potential inclusion bias, several centers conducted retrospective checks of their outpatient records to confirm that all eligible patients were considered for inclusion. Additionally, site monitoring and source data verification were performed by an independent clinical research organization to maintain data quality and adherence to inclusion criteria. To minimize inclusion bias and ensure comprehensive data collection, we will include all eligible patients according to pre-defined inclusion and exclusion criteria. Additionally, we will conduct a thorough review to confirm that no eligible patients were inadvertently excluded. Although the inclusion criteria might appear restrictive, as we specifically target high-risk patients with CCS, we believe this group is particularly relevant due to their persistent ischemic risk. Our objective is to provide real-world data, contrasting our findings with those of the COMPASS study. To ensure broad population representation and avoid underrepresentation of certain demographics or subgroups, we have selected centers from across the country.

A further limitation of this study is the relatively short follow-up duration of twelve months, which may not fully capture the long-term efficacy and safety outcomes of DPI in patients with CCS. Given the chronic and progressive nature of atherosclerotic cardiovascular disease, longer follow-up would be necessary to assess sustained ischemic protection, potential delayed bleeding risks, and treatment adherence over time. However, the 1-year timeframe was determined based on funding constraints imposed by the sponsor. Despite this limitation, we chose follow-up moments at 3 months and 1 year post DPI initiation to specifically monitor early adverse events—particularly bleeding—which typically emerge within the initial months of dual antithrombotic therapy. This design allows timely evaluation of tolerability and provides clinically relevant information on whether DPI can be safely continued or should be discontinued in real-world patients. Nonetheless, we recognize that late ischemic events and chronic safety concerns may not be fully captured. As such, an extended follow-up period is under consideration for future iterations of the registry, depending on feasibility and funding. This would enhance our understanding of the long-term net clinical benefit of DPI in this high-risk CCS population.

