### 2.2. Ethics and Informed Consent

Ethical approval for the study was granted by the non-WMO (WMO = Medical Scientific Research Act) Advisory Committee of a recognized Ethics Committee on behalf of the DCRF (‘Dutch Clinical Research Foundation’) for all sites after reviewing the protocol, site-specific informed consent forms, and other requested documents. Under Dutch law, this classification applies to research that does not involve interventions or procedures beyond standard clinical practice. As our study is observational and does not involve additional risk or burden to participants, formal review by a medical ethics committee under the WMO was not required.

Before participation, the treating physician informs the patient orally and in writing about the scope and purpose, rights, duties, and possible risks/benefits of the registry in lay language. Written informed consent from the patient is a prerequisite to participate in the registry. To maintain confidentiality, patients are identified only by their identification code. All patients will also receive a patient information form.

All study-related information will be stored securely at the study site. All participant information will be stored in locked file cabinets in areas with limited access. All reports, collected data, and process and administrative forms will be identified by a coded identification number only to maintain participant confidentiality. All records that contain names or other personal identifiers, such as locator forms and informed consent forms, will be stored separately from study records, identified by code number. All local databases will be secured with password-protected access systems. The study findings will be disseminated via publication of peer-reviewed manuscripts.

The results will be published irrespective of whether the findings are positive or negative.

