### 2.6. Data Collection and Follow-Up

The members of the study team prospectively gather data. During the baseline visit (T = 0), they collect historical data (demographic, laboratory—including parameters like hemoglobin, eGFR, and liver function—and clinical characteristics, including medication usage) from available medical records or through patient interviews if records are unavailable.

Primary and secondary endpoints are recorded at both 3-month and 1-year follow-up. The 3-month follow-up is conducted via telephone interview. Laboratory results are noted to the extent available within routine clinical practice, without performing additional study-related laboratory analyses. Patients are queried about adverse events, side effects of rivaroxaban, and any changes in their antithrombotic regimen (e.g., temporary cessation of aspirin, rivaroxaban, or both) and other medications. The time of final data collection is at one year, either through a face-to-face visit or via telephone contact (±30 days), or at 30 days in case of an early discontinuation of rivaroxaban therapy.

Potential reasons for premature study termination include consent withdrawal, loss to follow-up, or death of the patient. At this final observation, the patient’s condition and treatment assessment will be documented.

The treating physician determines the actual duration of treatment, which is not contingent on the initially intended treatment duration. In patients who permanently discontinue the combined treatment, discontinue rivaroxaban alone, or discontinue aspirin alone and who do not withdraw consent or experience a fatal adverse event during the observational period, the treating physician collects information on their survival status at the end of the study (i.e., 1-year ± 30 days after study inclusion).

A more detailed description of the variables collected during these visits is found in Table 3.

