### 2.8. Data Analysis

All statistical analyses were performed using IBM SPSS Statistics, version 28.0 (IBM Corp., Armonk, NY, USA).

The statistical analyses are explorative and descriptive. All analyses are performed for the total study population (overall analyses). The study period for analyses is defined as the time from the start of rivaroxaban until the end of the 1-year follow-up.

Descriptive statistics are performed for both primary and secondary study parameters. Continuous variables are expressed as mean ± standard deviation and as medians with minimum, maximum, 25th, and 75th percentiles. Categorical variables are presented by frequency tables (absolute and relative frequencies). Incidence proportions are computed together with corresponding exact 95% confidence intervals (CIs) for primary and secondary endpoints. Cumulative incidence of events or survival probabilities and 95% confidence intervals are estimated using Kaplan–Meier estimates for primary and secondary endpoints. The follow-up starts per definition on the date of the start of treatment and ends at the date of a first event, date of loss to follow-up, or date of end of the one-year study period, whichever comes first. The incidence of events over time is studied with the use of Kaplan–Meier methods. Patients who do not experience an event of interest by the end of their individual observation period are censored.

To control for confounding, the primary analyses will employ multivariable Cox proportional hazards regression models, with adjustment for prespecified baseline covariates known to influence clinical outcomes: age, sex, presence of diabetes mellitus, renal function, and CHA_2_DS_2_-VASc score. Model assumptions, including proportional hazards, will be assessed using Schoenfeld residuals. In addition, propensity score methods will be implemented as sensitivity analyses to further address confounding and potential selection bias. Propensity scores will be estimated using logistic regression models including the aforementioned covariates. These scores will be incorporated via adjustment for the propensity score as a covariate in the Cox model.

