**Inclusion Criteria**
Adult patient (≥18 years) Diagnosis of CAD and high risk of ischemic events Patients at high risk of ischemic events include, amongst others, the following: ○ CAD + PAD ○ CAD + recurrent myocardial infarction (previous myocardial infarction followed by a second) ○ CAD + diabetes mellitus (all types) ○ CAD + chronic kidney disease (eGFR 30–59 mL/min/1.73 m^2^) ○ CAD + heart failure (ejection fraction ≥ 30–50%) and NYHA class I or II ○ CAD + high CHA_2_DS_2_-VASc score (men > 3 or women > 4) Patients can only be enrolled in the study if the decision to treat with rivaroxaban plus aspirin has been made by the treating physician in advance and independent of study inclusion within 4 weeks prior to study inclusion. Patients who are willing to participate in this study (signed informed consent)

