**Exclusion Criteria**
Hypersensitivity/allergy and known contraindication to aspirin or rivaroxaban Patients with recent major bleeding, active bleeding, or one of the following: ○ History of major clinical bleeding or known coagulopathy ○ History of intracerebral mass, aneurysm, arteriovenous malformation, or hemorrhagic stroke Patients who received any organ transplant or await any organ transplant Patient with anemia (Hb < 6.0 mmol/L) Patient with active malignancy Patients with eGFR < 30 mL/min/1.73 m^2^ or undergoing dialysis Patients with liver failure accompanied with coagulopathy (Child-Pugh B and C) Patients with concomitant use of other anticoagulants or antiplatelet drugs Pregnant or lactating women Patients currently participating in another investigational drug or drug-coated device study

Abbreviations: CABG = Coronary Artery Bypass Grafting; CAD = Coronary Artery Disease; eGFR = Estimated Glomerular Filtration Rate; Hb = Hemoglobin; ISTH = International Society on Thrombosis and Haemostasis; MACE = Major Adverse Cardiovascular Event; PAD = Peripheral Artery Disease; PCI = Percutaneous Coronary Intervention.

**Table 2 jcm-14-04401-t002:** Primary endpoints.

Primary Efficacy Endpoints	Primary Safety Endpoints
Composite of the following events during one year: MACEs (composite of cardiovascular death, myocardial infarction or stroke) Clinically driven coronary, peripheral or carotid revascularization Stent thrombosis	Major bleeding according to ISTH during one year: Fatal bleeding Symptomatic bleeding into a critical organ Bleeding causing a fall in hemoglobin level of ≥2g/dL (1.24 mmol/L) or leading to transfusion of two or more units of whole blood or red cells.

Abbreviations: CABG = Coronary Artery Bypass Grafting; ISTH = International Society on Thrombosis and Haemostasis; MACEs = Major Adverse Cardiovascular Events; PCI = Percutaneous Coronary Intervention.

**Table 3 jcm-14-04401-t003:** Tabulated overview on study procedures and assessed variables.

Schedule Procedure	Initial Visit (Baseline)	Telephone Call/Report (3-Months FU)	Final Visit/Report at End of Observation (Last FU)
Date of informed consent	X		
Date of visit/report (day, month, year)	X	X	X
Demographic data	X		
Inclusion/exclusion	X		
Routinely collected laboratory data	X	X	X
Concomitant medication	X	X	X
Lifestyle	X		
Medical history	X		
Diagnosis of coronary artery disease	X		
Comorbidities	X		
Prior anticoagulation therapy *	X		

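### Treated patients found ineligible after enrolment may be dropped from the final analysis on a judgement about treatment, with no criterion, time limit or outcome blinding, and this is not reconciled with the stated analysis population

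*Protocol article*

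**What the plan says.** The rule stands in the selection-bias paragraph of the Discussion (section 4). It is triggered by eligibility: "In cases where a patient was included but later found to be ineligible, the treatment plan was re-evaluated". The consequence follows: "if DPI was deemed inappropriate, treatment was discontinued or the patient was excluded from the final analysis". The article presents this as one of the measures that limit selection bias.

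Four other places bear on it:

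- Section 2.8 on the analysis population: "All analyses are performed for the total study population (overall analyses". The population is not defined further, and removals for ineligibility are not mentioned.
- Section 2.8 on time at risk: "The follow-up starts per definition on the date of the start of treatment and ends at the date of a first event".
- Section 2.6 on patients who stop one or both drugs: unless they withdraw consent or die, "the treating physician collects information on their survival status at the end of the study". They are not removed.
- Table 1 on entry: the decision to treat must have been made "in advance and independent of study inclusion within 4 weeks prior to study inclusion". Its exclusion list includes "History of major clinical bleeding or known coagulopathy".

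**The concern.** By the time this rule can act, the patient has been prescribed the combination, has consented and, under section 2.8, has usually begun to accrue time at risk. Whether such a patient counts then depends on a judgement about the treatment, not only on a baseline fact. The word joining the two consequences is an *or*, so two patients with the same eligibility failure may end up differently: one stopped and followed to one year, the other deleted.

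The rule fixes the denominator and the event count of both primary endpoints, and a single-arm study has no comparator in which a similar bias might cancel. The safety endpoint is the more exposed. Table 1 excludes patients with recent, active or past major bleeding, coagulopathy, hemoglobin below 6.0 mmol/L, eGFR below 30, and liver failure with coagulopathy. Patients found to breach these criteria plausibly bleed more than the rest, so removing them would make the observed bleeding rate look lower than the rate among patients actually treated.

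The Discussion is written in the past tense, so some removals may already have taken place.

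**Working it through.** **1. The passages side by side**

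| Patient | Consequence stated | Where |
|---|---|---|
| Eligible, continues treatment | Analysed | 2.8 |
| Eligible, discontinues | Survival status collected at end of study; no removal | 2.6 |
| Found ineligible, combination judged appropriate | No removal stated; apparently kept | Discussion |
| Found ineligible, combination judged inappropriate | Treatment stopped, or patient removed; no criterion for which | Discussion |

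The third and fourth rows show that the analysed set is neither all enrolled patients (some are removed) nor all eligible patients (some ineligible ones stay). Sections 2.4 and 2.8 deal with dropout, censoring and missing data. They do not deal with ineligible patients and so do not settle the matter.

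**2. Size**

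The plan gives no number of removals and no bleeding rate among those removed, so there is no figure of its own to reproduce. What follows is an illustration.

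Inputs from the article:
- Major bleeding of 3.1% with the combination in the earlier randomised trial (Introduction).
- Follow-up of 23 months in that trial against 12 months here (section 2.4).
- Planned N = 1000 (section 2.4).

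Assumptions: constant hazard; *k* = 20 patients removed (or 10); the bleeding risk of those removed.

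Twelve-month risk:

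- Monthly hazard = −ln(1 − 0.031)/23 = 0.001369
- 12-month risk = 1 − exp(−12 × 0.001369) = 1.63%, or about 16 events in 1000. The steps below use 16/1000 = 1.60%.

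Rate after removal = (16 − events removed)/(1000 − *k*):

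| Removed | Assumed risk in those removed | Events removed | Rate after removal | Relative change |
|---|---|---|---|---|
| 20 | Same as the rest, 1.6% | 0.32 | 15.68/980 = 1.60% | none |
| 20 | Twice, 3.2% | 0.64 | 15.36/980 = 1.57% | −2% |
| 20 | Three times, 4.8% | 0.96 | 15.04/980 = 1.53% | −4% |
| 20 | 20% (4 bleeds) | 4 | 12/980 = 1.22% | −23% |
| 10 | 20% (2 bleeds) | 2 | 14/990 = 1.41% | −12% |

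The 20% rows are extreme: 20/1.6 = 12.5 times the baseline risk. The exact 95% interval for 16/1000 is 0.92% to 2.59%, so even 1.22% lies inside it.

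**3. Other event rates**

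Section 2.4 expects most endpoints in 1% to 5% of patients. With 20 removed and a 20% event share among them, a 1% endpoint becomes (10 − 4)/980 = 0.61%, a 3% endpoint (30 − 4)/980 = 2.65%, and a 5% endpoint (50 − 4)/980 = 4.69%. The relative effect is largest for rare endpoints.

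**The case against.** The strongest reply is that the trigger is ineligibility, found through audits and source data verification, and that the judgement on treatment applies only to patients already found ineligible. The criteria are largely baseline characteristics, and a bleed during follow-up does not by itself make a patient ineligible at entry. Removing patients for baseline ineligibility, judged without sight of outcome, redefines the population and does not in itself bias the estimate for that population. All of this is correct, but the Discussion does not state that rule. It adds a treatment judgement, leaves the consequence open, and sets neither a time limit nor blinding.

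Four stronger readings are tempting and are not supported:

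- *The exclusion is outcome-dependent.* A reader might infer this, because a bleed could prompt the chart review that uncovers the ineligibility. No passage ties removal to an observed endpoint. Outcome dependence is possible, not shown.
- *The Discussion contradicts section 2.8.* The total study population is undefined there, and the bracketed words may only mean the whole cohort as opposed to subgroups. The two places are unreconciled, not flatly opposed.
- *Removal defeats the study's aim.* The Discussion describes the target as a guideline-eligible cohort, not an unselected one, so an eligible-patient analysis is a legitimate choice.
- *The rule conflicts with section 2.2.* The words there, "research that does not involve interventions or procedures beyond standard clinical practice", describe a legal class of research. Section 2.6 leaves treatment duration to the treating physician, and the Discussion does not say that re-evaluation involved any added procedure.

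It is also fair to say that the study is descriptive, with no hypothesis test or decision threshold, so a modest shift would not overturn a formal conclusion.

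**Conclusion.** The point holds as a defect in a stated rule, not as an omission that an analysis plan might fill. The article allows discretionary removal of treated patients after enrolment, with no criterion for the choice, no time limit and no blinding to outcome, and it does not square this with sections 2.6 and 2.8. The rule is potentially outcome-dependent, and the likely direction for major bleeding is downward.

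The size cannot be known from the article. Under a constant hazard and 20 assumed removals, it runs from no effect at average risk, through 1.57% at twice the baseline risk, to 1.22% in a deliberately extreme case, against a starting 1.60%. Realistic excess risks give small shifts; a large one needs removals that are strongly enriched for bleeds. The article's suggestion that this procedure mitigates selection bias cannot be relied on, since discretionary removal of exposed patients can introduce such bias. The point should be fixed, but it does not by itself undermine the study.

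**What to change.** - Replace the rule in the Discussion so that no patient is removed from analysis on a judgement of whether treatment was appropriate. No view is taken here on the treatment decision itself.
- Analyse all consented patients who started rivaroxaban plus aspirin, whatever later eligibility findings show.
- Present alongside it an eligibility-confirmed set, defined only by objective baseline criteria and judged by someone blind to outcome. State in advance which of the two is primary; either can be defended.
- Report the number of ineligible patients, with the reason and the events for each, and restore any already removed to the all-treated analysis.
- Define the total study population in section 2.8, and reconcile it with section 2.6 and the Discussion.

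The cost is a few sentences of wording, a blinded eligibility review and one additional set of tables. If patients have already been removed, their outcomes must be recovered as far as consent and the records allow.
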